## Abstract

**Introduction::**

Rehabilitation after anterior cruciate ligament (ACL) reconstruction is critical to patient outcome. Despite its importance; however, hospital-based rehabilitation is limited, with barriers, including distance and cost. With recent technological advancements, wearable devices have actively been used to address these barriers. In this study, we propose a randomized controlled trial protocol investigating the efficacy and feasibility of home-based rehabilitation after ACL reconstruction using a smart wearable device providing electrical stimulation that allows knee exercise.

**Methods and analysis::**

This is a protocol proposal for a prospective, single-center, randomized, controlled study. We plan to recruit adults discharged after ACL reconstruction; the recruited subjects will be randomly allocated to 1 of 2 groups, using a computer-generated randomization method: the intervention (n = 20) or control group (n = 20). The intervention group will receive a 6-week home-based rehabilitation program using smart wearable device. The control group will undergo a 6-week self-exercise program as normal. The following outcomes will be assessed at baseline, 2 weeks, and 6 weeks post the 6-week intervention program: quadriceps strength of the affect side as measured by a dynamometer (primary outcome); range of motion; root mean square of quadriceps muscle using surface electromyography; knee function using questionnaire; quality of life; subject's satisfaction score using questionnaire; frequency and duration of exercise; and knee pain. An intention-to-treat analysis will be conducted for the primary outcome.

**Discussion::**

This study is a prospective, single-center, randomized, controlled study. This study aims to research the feasibility and efficacy of a 6-week, structured home-based rehabilitation program for patients after ACL reconstruction using a smart wearable device. The findings of this study will help to establish a home-based rehabilitation program to better recovery in patients with ACL reconstruction.

**Trial registration number::**

This protocol was registered in ClinicalTrials.gov, under the number NCT04079205.

## Introduction

1

Injuries and surgical interventions of the knee often lead to weakness, pain, and reduced function of the quadriceps muscle.^[1,2]^ Rehabilitation to restore the range of motion and strength of the quadriceps muscle is essential for better postoperative outcomes.^[3,4]^ However, according to a previous study, only 35% to 76% of patients comply with the exercise regimens as prescribed.^[5]^ Reasons for such a low compliance may include physical and personal problems and, more importantly, lack of patient motivation.^[6,7]^ In addition, repetitive rehabilitation exercises may be boring, and routine outpatient care may be too burdensome on patients, requiring great effort and increased cost. Moreover, lack of professional facilities and/or manpower may also contribute to the problem of low compliance. These problems collectively can ultimately result in reduced compliance and thus increase the overall rehabilitation period and reduce the effectiveness of rehabilitation treatment.^[8,9]^

To improve the overall treatment outcomes, new rehabilitation techniques that focus primarily on improving patient motivation, and thereby compliance, may be necessary. To such effort, various medical devices and rehabilitation programs have been developed, manufactured, and researched. Approaches that incorporate games or gaming techniques derived from the video game industry have been presented as inexpensive and promising alternatives to regular physical therapy or home-based rehabilitation exercises.^[10]^ In recent years, much attention has been focused on combining games and wearable technology into exercise programs, allowing patients to have more fun and an immersive experience while getting the benefits of exercise. By removing the sense of obligation by associating exercise with fun, this combination of game and wearable technology with exercise has the ability to improve patient compliance while reducing the aforementioned burden of treatment.^[11]^ Furthermore, data acquired from various sensing system in wearable devices and game scoring systems can provide more objective monitoring, which could be used to provide better feedback.^[12,13,14]^

We propose an exercise program that will incorporate wearable technology with gaming components. The wearable device that will be used in this study (exoRehab, EXOSYSTEMS Inc., Seongnam, South Korea) can measure the range of motion and strength of the knee joint. This will allow us to measure whether the exercise program can increase the range of motion and strength of the knee after the operation. Moreover, this wearable technology will also make it possible to provide biofeedback to patients to verify whether there is sufficient contract to improve knee strength by measuring the surface electromyography (EMG). Previous studies have shown that biofeedback through the surface EMG improves not only knee extension,^[15]^ but also muscle strength of the quadriceps muscle.^[16]^ In addition to providing biofeedback to patients, it is possible to provide neuromuscular electrical stimulation and rehabilitation. Surface EMG-triggered neuromuscular electrical stimulation improves knee extension via increasing the active range of motion.^[17]^ Neuromuscular electrical stimulation therapy has also been shown in previous studies to show significant improvements in muscle strength and function outcomes of the quadriceps muscles.^[18,19]^

Information from the device can be used by doctors and therapists to enhance the understanding of patient compliance and progress of knee rehabilitation, which may be useful to determine a unique, personalized treatment goal tailored to each patient. We hypothesize that the incorporation of games and wearable technology into an exercise therapy program will improve patient motivation and compliance. This approach is expected to overcome and address the shortfalls of current rehabilitation treatment methods and promote a wave of new in-home rehabilitation programs.

## Methods and analysis

2

### Trial design

2.1

This study is a randomized controlled single-center, assessor-blinded, parallel-group clinical trial conducted at the Seoul National University Bundang Hospital, South Korea. This study was approved by the local Institutional Review Board (IRB No. B-1806-475-006) and registered in ClinicalTrial.gov (NCT04079205). The recruited participants will provide written informed consent before participation. The schedule of enrolment, interventions, and assessments is outlined in Figure 1.

**Figure 1 F1:**
[figure not shown]
Schedule of enrolment, interventions, and assessments. T0: enrollment; T1: baseline variables; T2: allocation; T3: 2-wk after intervention initiation; T4: 6-wk after intervention initiation (endpoint of intervention, post-intervention evaluation); AROM = active range of motion, IKDC = International Knee Documentation Committee (IKDC questionnaire), KOS-ADLS = knee outcome survey activities of daily living scale, Lysholm = Lysholm knee scoring scale, PROM = passive range of motion, QoL = quality of life, RMS = root mean square, sEMG = surface electromyography, VAS = visual analog scale.

### Trial status

2.2

Data collection is currently ongoing at the time of submission study.

### Participants

2.3

Patients who underwent anterior cruciate ligament (ACL) reconstruction at the Seoul National University Bundang Hospital will currently being screened and recruited. Subject's eligibility for inclusion will be determined during the screening process. If eligible, subjects will be assigned to 1 of the 2 groups – intervention or control group – according to the randomization method. Personal data will be numerically coded and stored in a separate database. Informed consent and all study information will be passed on to all participants. Before data collection, participants must sign the informed consent form.

#### Eligibility criteria

2.3.1

##### Inclusion

2.3.1.1

(1)Subjects who underwent ACL reconstruction surgery(2)Nineteen years of age or older, with the ability to provide their own consent

##### Exclusion (any of the following)

2.3.1.2

(1)History of surgery or traumatic injury to the uninvolved lower extremity(2)Complication after ACL reconstruction surgery(3)Dermatological conditions affecting the thigh(4)Body mass index of greater than 40 kg/m^2^(5)Implanted pacemakers or defibrillators(6)Significant neurologic impairments(7)Other unstable lower-extremity orthopedic conditions(8)Initiated rehabilitation at another facility before the first physical therapy session at our facility(9)Other lower limb impairment affecting its function(10)More than 1 surgery for the treatment of torn ACL

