### Randomization and blinding

2.4

Participants in this trial will be randomly assigned in a ratio of 1:1 to either the control group (home-based self-exercise program) or the intervention group (home-based exercise program using device). Participants will be allocated to 1 of the 2 groups via blocked randomization with variable size blocks to ensure an equal number of participants in both groups. This method reduces selection bias, especially in studies with small sample sizes.^[20]^ Allocation will be concealed using sequentially numbered opaque envelopes. These envelopes are stored in a lock-sealed location. A researcher without direct contact with patients will select and open the envelope in the presence of a physiotherapist to see the assignment number. This randomized assignment number will then be recorded in the case record form, and the study will be performed according to the assigned group. Due to the characteristics of this test method, the outcome assessor will also be blinded to group allocation. Once the intervention is completed, the researcher responsible for the statistical analysis will receive an Excel spreadsheet with the necessary data without any identifiable parameters. A flow diagram of the study is shown in Figure 2.

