#### Device

2.5.1

Subjects assigned to the intervention group will be provided with wearable device (Fig. 3A). The main unit of device consists of 3 parts: the thigh part, shin part, and connecting part. The program for exercise, electrical stimulation, and measurement are carried out through a separate tablet application. The tablet and main unit are connected via Bluetooth. The thigh and thin parts each have

(1)electrical stimulation electrodes for neuromuscular electrical stimulation (NMES),(2)sensors for measuring muscle contraction through surface EMG, and(3)sensors for measuring of knee joint angles.

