#### Intervention group

2.5.2

Subjects will be educated on using the device for exercise by a physical therapist before discharge, and exercise will be performed using the device at home after discharge. Treatment may vary depending on patient's condition, but it should generally include the following:

Range of motion exercise should be repeated 3 times a day for 10 times, and it should be limited to the allowable range (Fig. 3B). The allowable range is 60° for 2 weeks, 90° for 4 weeks, and 120° for 6 weeks.

The exercises program includes quadriceps setting exercise (10 minutes, 3 times during a day), a straight leg raises exercise (5 minutes, 10 times during a day), and an ankle pump exercise (4 minutes, 10 times during a day) for 2 weeks after the operation, followed by a standing side-to-side weight shift exercise (2 minutes, 3 times during a day), a partial squat with chair exercise (2 minutes, 3 times during a day), and a heel raises exercise (2 minutes, 3 times during a day). If tolerable with this exercise program, the subject is allowed to gradually increase the frequency of the exercises. The device is designed to measure the patient's maximum voluntary isometric contraction (MVIC) before beginning a workout. To allow the patient to exercise correctly and to provide a game-like experience, the threshold will be set to 66% of MVIC, and it will be considered a count of 1 when a force above the threshold is applied in the quadriceps setting exercise program (Fig. 3C). Exercise instructions will be provided as part of pre-discharge education, and description, picture, and video of the exercises will be attached to the machine for reference. The minimum recommendation for training is about 10 minutes of quadriceps setting exercise, 3 times a day. If desired, they are allowed to practice more often.

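### The skin exclusion covers only the thigh, but the device as described also has a worn shin part carrying electrodes and sensors

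*Protocol article*

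**What the plan says.** Section 2.3.1.2 of the protocol article lists ten exclusions. The third, "Dermatological conditions affecting the thigh", is the only one about skin.

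Section 2.5.1 describes the hardware: "The main unit of device consists of 3 parts: the thigh part, shin part, and connecting part". It goes on: "The thigh and thin parts each have" three kinds of component, namely electrodes for neuromuscular electrical stimulation (NMES), "sensors for measuring muscle contraction through surface EMG", and sensors for the knee angle. The word before *parts* is evidently a misprint for *shin*, since the section has just named the three parts and no other fits.

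On exposure, the abstract says: "The intervention group will receive a 6-week home-based rehabilitation program using smart wearable device". Section 2.4 states that participants are "randomly assigned in a ratio of 1:1". Section 2.5.2 has the device group exercise at home with the device. It also places the purpose of stimulation on the thigh: the patient contracts the quadriceps, and the current is set to give a full quadriceps contraction. Section 2.6.2 takes the outcome EMG from three quadriceps muscles.

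**The concern.** Control exercises are the same apart from the device (section 2.5.3), so the device is the evident reason for a skin exclusion, although the article does not say so. If skin under the thigh part has to be sound, the same reasoning applies to skin under the shin part, which is described as carrying the same components. The rule screens one of the two sites.

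What is at stake is the safety of individual participants. Someone with, for example, active skin disease on the shin could enter the trial and wear the shin part at home for weeks. The point does not concern power, error rates, bias or the estimand.

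**Working it through.** No figure in the plan bears on this point, so the check is a comparison of the eligibility list with the device description.

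**Step 1. Which limb parts carry electrodes and sensors (section 2.5.1)?** As written, two: thigh and shin. The connecting part is not said to carry any.

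**Step 2. Which of these does the skin exclusion cover (section 2.3.1.2)?** One of two, the thigh.

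**Step 3. Does another criterion close the gap?** Take a patient with shin skin disease, normal limb function and no surgical complication.
- (1) concerns earlier surgery or trauma to the other leg: does not apply.
- (2) concerns complications of the reconstruction: would catch a wound problem, but not unrelated skin disease.
- (4), (5) and (6) concern body mass index, implanted cardiac devices and neurological impairment: do not apply.
- (7) concerns unstable orthopaedic conditions of the leg: does not apply.
- (8) and (10) concern rehabilitation begun elsewhere and repeat ligament surgery: do not apply.
- (9) concerns lower-limb impairment that affects function: does not apply, because function is normal.

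The two inclusion criteria (the surgery; age 19 or over with capacity to consent) contain no skin check. The patient is eligible. Count: 10 exclusions, 1 on skin, 0 naming the shin.

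**Step 4. Chance of being assigned the device.** 20 of 40 participants are allocated to it: 20/40 = 0.5 for each such patient. This is only the allocation ratio and does not measure harm.

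**Step 5. What wear can be inferred?** Section 2.5.2 says "Range of motion exercise should be repeated 3 times a day for 10 times" and has the group exercise with the device. It is reasonable to take the shin part as worn then, since the knee angle is measured across the joint. The same section recommends NMES at least 3 times a day, but describes it as quadriceps stimulation. It is therefore not used here as evidence of current applied to the shin.

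**Step 6. Do later safeguards substitute for screening?** Therapist training, patient-controlled intensity, the visits at 2, 4 and 6 weeks and the monitoring committee all come after randomisation. Withdrawal for discomfort or medical reasons (section 2.7) and discontinuation when underlying disease worsens (section 2.8) act only once the patient has been exposed. They limit harm, but none is an eligibility check.

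The article gives no prevalence of shin skin disease and no contact time for the shin part, so no patient count or risk is offered.

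**The case against.** The strongest reply is that the point rests on the word *each* in one loosely worded sentence that also contains a misprint. Wherever the article describes use, stimulation, biofeedback and outcome EMG concern the quadriceps. No use for shin electrodes or shin EMG is given, and only the angle sensors plainly need both parts. The list may describe the unit as a whole, and the figure showing the device in wear is not available to settle it. On that reading the thigh criterion matches the skin that is stimulated and recorded. Section 2.5.2 also lets treatment vary with the patient's condition, and a therapist teaches device use before discharge, so a visible shin problem might well be noticed.

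Much of this stands. It rules out two stronger readings that a reader might draw. One is that shin skin is stimulated several times a day for 6 weeks; the NMES schedule does not support that. The other is that the article contradicts itself; it does not, because a thigh criterion fits the treatment target and the EMG outcome sites.

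What does not fall away is that a shin part is worn and, as the text stands, carries electrodes and sensors, while the only skin criterion stops at the thigh. Nor is this a detail that a condensed article leaves to the full protocol: the criterion is stated, with an explicit limit to one site. The therapist's discretion is helpful but does not replace an entry criterion.

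**Conclusion.** The point holds as a minor participant-safety matter. Exclusion (3) is set narrower than the skin area on which section 2.5.1 places hardware, so a patient with shin skin disease and normal limb function could be randomised to wear the device.

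This rests on two assumptions: that the misprinted word means *shin*, which the preceding description of the parts supports, and that the shin part touches the skin, which electrodes and EMG sensors imply but the article does not state.

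The risk cannot be quantified, and in a trial of 40 the number of patients affected is probably small. There is no consequence for the sample size, the significance level or the analysis.

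**What to change.** Reword exclusion (3) to: *dermatological conditions at any skin site in contact with the device (thigh or shin)*. Apply it to every candidate before randomisation, so that both arms are drawn from the same population.

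The cost is one phrase in the eligibility list, checked at the existing screening, and possibly a few extra screen failures.

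The sponsor should first confirm what the shin part carries. If it has no electrodes and does not touch the skin, exclusion (3) can stay and the device description in section 2.5.1 should be corrected instead.

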### Randomization and blinding

2.4

Participants in this trial will be randomly assigned in a ratio of 1:1 to either the control group (home-based self-exercise program) or the intervention group (home-based exercise program using device). Participants will be allocated to 1 of the 2 groups via blocked randomization with variable size blocks to ensure an equal number of participants in both groups. This method reduces selection bias, especially in studies with small sample sizes.^[20]^ Allocation will be concealed using sequentially numbered opaque envelopes. These envelopes are stored in a lock-sealed location. A researcher without direct contact with patients will select and open the envelope in the presence of a physiotherapist to see the assignment number. This randomized assignment number will then be recorded in the case record form, and the study will be performed according to the assigned group. Due to the characteristics of this test method, the outcome assessor will also be blinded to group allocation. Once the intervention is completed, the researcher responsible for the statistical analysis will receive an Excel spreadsheet with the necessary data without any identifiable parameters. A flow diagram of the study is shown in Figure 2.

**Figure 2 F2:**
[figure not shown]
Flow diagram of the study.

### Intervention

2.5

After signing the informed consent forms, eligible subjects will be randomly assigned to 1 of the 2 groups: the intervention group or control group. All subjects will visit the outpatient clinic at 2 weeks, 4 weeks, and 6 weeks after the initiation of the intervention. Exercise status will be checked at these visits, and subjects will be encouraged to continue performing the exercise program.

#### Device

2.5.1

Subjects assigned to the intervention group will be provided with wearable device (Fig. 3A). The main unit of device consists of 3 parts: the thigh part, shin part, and connecting part. The program for exercise, electrical stimulation, and measurement are carried out through a separate tablet application. The tablet and main unit are connected via Bluetooth. The thigh and thin parts each have

(1)electrical stimulation electrodes for neuromuscular electrical stimulation (NMES),(2)sensors for measuring muscle contraction through surface EMG, and(3)sensors for measuring of knee joint angles.

**Figure 3 F3:**
[figure not shown]
A smart wearable knee exercise and electrical stimulation device. (A) User wearing device; (B) one of the games for range of motion exercise; (C) screenshot of subject exercises using the bio-feedback – the left side of the screen shows the threshold; (D) screenshot of the neuromuscular electrical stimulation setting.

In addition, data pertaining to subject's usage behavior and contents are stored on device, which can be used to analyze the progress of the knee rehabilitation program and to help set personalized treatment goals.

#### Intervention group

2.5.2

Subjects will be educated on using the device for exercise by a physical therapist before discharge, and exercise will be performed using the device at home after discharge. Treatment may vary depending on patient's condition, but it should generally include the following:

Range of motion exercise should be repeated 3 times a day for 10 times, and it should be limited to the allowable range (Fig. 3B). The allowable range is 60° for 2 weeks, 90° for 4 weeks, and 120° for 6 weeks.

The exercises program includes quadriceps setting exercise (10 minutes, 3 times during a day), a straight leg raises exercise (5 minutes, 10 times during a day), and an ankle pump exercise (4 minutes, 10 times during a day) for 2 weeks after the operation, followed by a standing side-to-side weight shift exercise (2 minutes, 3 times during a day), a partial squat with chair exercise (2 minutes, 3 times during a day), and a heel raises exercise (2 minutes, 3 times during a day). If tolerable with this exercise program, the subject is allowed to gradually increase the frequency of the exercises. The device is designed to measure the patient's maximum voluntary isometric contraction (MVIC) before beginning a workout. To allow the patient to exercise correctly and to provide a game-like experience, the threshold will be set to 66% of MVIC, and it will be considered a count of 1 when a force above the threshold is applied in the quadriceps setting exercise program (Fig. 3C). Exercise instructions will be provided as part of pre-discharge education, and description, picture, and video of the exercises will be attached to the machine for reference. The minimum recommendation for training is about 10 minutes of quadriceps setting exercise, 3 times a day. If desired, they are allowed to practice more often.

NMES will be performed with an isometric exercise in sitting position with the knee extended. The patient will first contract the quadriceps muscles, and electrical stimulation will begin only when the force exceeds 75% of MVIC. The device delivers biphasic rectangular waveform pulses (pulse duration 400 μs, frequency of impulses 2500 Hz, train of pulses frequency 50 Hz). A total of 15 contractions is sustained for 15 seconds (inclusive of 2 seconds ramp up and down), each with 50 seconds off time. The total time for 1 set of NMES is about 22 minutes. Patients will be recommended to use NMES at least 3 times a day, about 66 minutes per session. The amplitude should be set at an intensity that is high enough to produce a full, sustained contraction of the quadriceps with visual and/or palpable evidence. The initial intensity will be set for each subject when a physical therapist trains and explains the device and exercise. The stimulus intensity will be increased further to maximum subject tolerance. As the rehabilitation program progresses, the intensity of NMES will be changed as the subject's maximal tolerable level (Fig. 3D). Exercise data using the device will automatically be stored on the device and will be used for analysis.

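### The NMES schedule has two separate inconsistencies: the stated timings give a 16.25-minute set, not about 22 minutes, and 66 minutes is given per session although it equals three 22-minute sets

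*Protocol article*

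**What the plan says.** The protocol article, section 2.5.2 (Intervention group), describes the stimulation in one paragraph:

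- Contraction timing: "A total of 15 contractions is sustained for 15 seconds (inclusive of 2 seconds ramp up and down), each with 50 seconds off time".
- Set length: "The total time for 1 set of NMES is about 22 minutes".
- Frequency and session length: "Patients will be recommended to use NMES at least 3 times a day, about 66 minutes per session".
- Trigger: the patient contracts first, and "electrical stimulation will begin only when the force exceeds 75% of MVIC". No time is given for this step.

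The number of sets in a session is not stated, and no other section gives a daily NMES total. Section 2.5.3 (Control group) says that controls do the same exercises without the device, so they have neither biofeedback nor electrical stimulation. Section 2.6.2 lists exercise frequency and duration, taken from the device or a logbook, as a secondary outcome. Section 2.2 says that data collection is under way.

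**The concern.** NMES is part of what separates the two arms, so these figures describe the experimental treatment itself. They were printed side by side and can be checked against each other. Two checks fail: contraction timing against set length, and set length and daily frequency against session length.

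Three things are at stake.

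- **Treatment delivered.** A therapist or participant working from this paragraph could aim for three sets a day or for three times as many.
- **Reading the usage data.** Logged NMES minutes can be reported as they stand, but they can be compared with the recommended minimum only if that minimum has one value. A participant who logs 66 minutes a day meets one reading in full and a third of the other. Non-compliance with the intervention is a ground for discontinuation in section 2.8 and is reportable under section 2.9.
- **Describing the intervention afterwards.** A published result cannot be replicated from a schedule that does not multiply out.

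**Working it through.** **Inputs, all from section 2.5.2:** 15 contractions per set; 15 s on, ramps included; 50 s off; set of about 22 min; at least 3 uses a day; about 66 min per session.

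**Check 1: set length**

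Set time = contractions × (on + off).

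- As written: 15 × (15 + 50) s = 975 s = 16.25 min.
- Last rest dropped: 15 × 15 + 14 × 50 = 925 s = 15.42 min.
- 2 s up and 2 s down added on top of the 15 s, against the text: 15 × (19 + 50) = 1,035 s = 17.25 min.

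The stated 22 min is not reproduced by any of these. It exceeds 16.25 min by 5.75 min (22/16.25 = 1.35), which is more than rounding explains.

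What would be needed to reach 22 min (shown for size only, not as proposals):

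- 22 × 60 / 15 = 88 s per cycle, which is 88 − 65 = 23 s of extra time per contraction, or an off time of 88 − 15 = 73 s; or
- 22 × 60 / 65 = 20.3 contractions (20 contractions give 20 × 65 s = 21.7 min).

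**Check 2: session or day**

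- Three sets at the stated set length: 3 × 22 = 66 min. The printed 66 is reproduced exactly as the total for three sets.
- As written, 66 min per session and three sessions: 3 × 66 = 198 min a day.
- Ratio: 198/66 = 3.

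Over 42 days the two readings come to 66 × 42 / 60 = 46.2 hours and 198 × 42 / 60 = 138.6 hours. Both are minima, because the frequency is given as a lower bound.

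**Effect on stimulation time, as opposed to clock time**

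Stimulation time per set is 15 × 15 s = 225 s = 3.75 min, however long the set lasts.

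| Reading | Sets per day | Contractions per day | Stimulation time per day |
|---|---|---|---|
| 66 min is the daily total | 3 | 45 | 3 × 3.75 = 11.25 min |
| 66 min is one of three sessions, each of three 22-min sets | 9 | 135 | 9 × 3.75 = 33.75 min |

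If the count and on-time hold, check 1 affects elapsed time only. Check 2 changes the exposure itself.

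**The case against.** The strongest reply is that both discrepancies have plausible innocent explanations.

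On set length, 16.25 min counts only on-time and off-time. Stimulation is triggered by the patient, so elapsed time must exceed that sum, and the device also measures MVIC before a workout. About 23 s per contraction would close the gap, and 22 is given only as an approximate total. This stands in part: the set-length figures are not shown to be impossible together. But the article times neither step and does not attribute the difference to them, so a reader cannot recover 22 min from what is stated.

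On session length, the exact match 3 × 22 = 66 makes a one-word slip likely. That stands as a likely explanation, but the printed wording still says the other thing and nothing else in the article settles it.

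Other points on that side also stand. The figures are minimum recommendations, and section 2.5.2 allows treatment to vary. A therapist trains each participant, and no document shows that anyone was told 198 minutes. Section 2.6.2 does not define adherence as a ratio to a prescribed NMES amount. Actual use is stored on the device and can be reported.

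A reader might go further and infer that the daily dose is undefined by a factor of about four, from 3 × 16.25 = 48.75 min up to 198 min (198/48.75 = 4.06). The documents do not support that as a single range. It multiplies two unrelated discrepancies, one of 1.35-fold and one of 3-fold. The first does not change stimulation time if 15 contractions of 15 s hold.

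**Conclusion.** The point holds as two separate inconsistencies in one paragraph.

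1. The stated timings give 16.25 min per set (15.42 to 17.25 min across readings of the ramps and last rest), against about 22 min. The gap of 5.75 min depends on something the article does not state. It is a gap in elapsed time, and the documents do not go so far as to show that the figures cannot all be true.
2. The minimum daily time is 66 or 198 min, a three-fold difference, depending on whether 66 min belongs to the day or to each of three sessions. This is the more consequential of the two because it changes the number of contractions. The nine-set reading assumes that a 66-minute session is made up of 22-minute sets, which the article does not say.

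Which figures are right cannot be decided from the document. The sample size (section 2.10.1), the primary outcome (section 2.6.1) and the analysis model (section 2.11) do not use these figures and are not affected.

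**What to change.** The sponsor should reconcile the contraction count, on and off times, any trigger or set-up time, set length, sets per session and daily frequency in section 2.5.2 so that they multiply out, and should state separately what is per set, per session and per day. The clinical team decides which figures are right.

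The reconciled figures should then go into the pre-discharge training material and be the reference for any comparison of logged NMES use with the recommended amount under section 2.6.2. Because data collection has started, the sponsor should also check the device logs and what participants already enrolled were told, and record any difference between them.

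The cost is a correction to one paragraph and the training material, plus a review of data that the device already stores. No change to the design, sample size or primary analysis is needed.
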